**Discussion:**

This is the first adequately powered RCT including normal weight adolescents, evaluating a reasonably long period of provision of and exposure to active games. Next, strong elements are the incorporating motivational elements for active game play and a comprehensive process evaluation. This trial will provide evidence regarding the potential contribution of active games in prevention of excessive weight gain in adolescents.

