### Sample size

Sample size calculation is performed to estimate how many adolescents should be included to detect a significant difference of 0.5 kg excess body weight between the intervention and control condition during the follow-up measurements (primary analysis). The 0.5 kg excessive weight gain is based on calculations in adults, because calculations for adolescents were lacking at that time. Adult individuals may gain on average 0.5 kg excess body weight per year, which results from an energy imbalance of only 70 Kcal per week per year [43]. We computed, based on energy expenditure studies, that an excess weight gain of 0.5 kg, may be prevented by substituting one hour per week of non-active gaming by playing active games [45]. To have sufficient power to detect a clinically relevant difference in excess weight gain of 0.5 kg (SD = 1.5 kg) between the intervention and control condition during follow up, with a power of 0.80, alpha .05 and an intraclass correlation coefficient (ICC) for within-subject clustering of observations of 0.7, 99 participants in each condition are needed. Taking into account an anticipated drop-out of 20%, a total of 119 adolescents per condition needs to be recruited.

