### Measurements

#### Adolescents’ anthropometrics (T_0_, T_4m_, T_10m_) (primary outcomes)

Adolescent’s anthropometric measures: height, weight, waist and hip circumferences and skinfolds thickness are performed at T_0_, T_4m_ and T_10m_ on pre-scheduled days at central places in the same four cities where we recruited the participants. These measurements take place at a site close to where the participants live (a museum, school or soccer stadium). Adolescents who are incapable to visit during the pre-scheduled days are measured at home. Trained research assistants conduct the measurements in an accurate manner according to a standardized protocol.

Height is measured to the nearest 0.1 cm using a Seca type 214 stadiometer with adolescents standing on bare feet and their head in the Frankfort plane. Weight is measured on bare feet with a calibrated electronic scale (SECA) with an accuracy of 0.1 kg. Adolescents are allowed to wear light indoor clothing, such as a t-shirt and shorts/short pants, and are asked to remove belt or any other heavy objects of use such as phone, keys or wallet. BMI (kg/m^2^) is calculated by dividing weight (kg) by height squared (m^2^). Next, BMI-SDS is determined using the data from the fourth Dutch growth study among children of 1997 as reference [3] employing the Growth Analyser software (https://www.growthanalyser.org/). Waist and hip circumference are measured with a tape measure (brand Jobst) to the nearest 0.1 cm. For waist circumference we also determine the SDS values using the same reference group and software as for BMI. Skinfolds are measured with an accuracy of 0.2 mm using four-site skinfold measures (triceps, biceps, subscapular and suprailiac) with a Harpenden skinfold calliper [49]. For hip circumference and skinfold thickness valid Dutch reference data to calculate SDS scores are not available.

At least two readings of each measurement (weight, height, waist/hip circumference and skinfolds) are obtained to deal with intra-observer variability, and the mean of the two measurements is used for analyses. If the two readings differ more than 1 cm for height, more than 0.2 kg for weight, more than 1 cm for waist and hip circumference, more than 1 mm for skinfolds, a third measurement is taken. In case of three measurements, the outlier of the three will be excluded.

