### Statistical analyses

First descriptive analyses are performed and data are checked for a normal distribution. Subsequently, control group and intervention group are described on baseline for demographics and outcome measures. Next, the effects of the intervention on all outcomes are evaluated by multilevel analyses. In the primary analyses, we analyze those participants which have at least one follow-up measurement in the groups they were randomized to. As a sensitivity analyses we will also impute follow-up measurements for persons with only a baseline measurement using multiple imputation with chained equations (intention to treat). Two models are constructed for each outcome measure: *model 1* adjusts for the baseline value of the outcome measure; and *model 2* additionally adjusts for demographics (age, sex, ethnicity and adolescent educational level) that are expected to associate with the outcome [3-5]. Second, analyses are performed according to the per protocol principle including the participants in the intervention group who played the Move games at least one hour per week. Adherence to protocol will be defined for each follow-up measurement separately, based on the question in the questionnaire assessing use of Move games (in hours per week) at T_1m_, T_4m_ and T_10m_. Again, two models are constructed for each outcome measure: *model 1* adjusts for baseline outcome measure; and *model 2* adjusts for demographics (age, sex, ethnicity and adolescent educational level) that are expected to associate with the outcome [3-5].

Additionally, a sensitivity analyses is performed by constructing all the models excluding the more extreme values on sedentary screen time (e.g. > 12 hours per day of non-active time). Further, if feasible (i.e. if the number of participants allows), explorative analyses are performed to check whether sex, age, adolescent educational level and ethnicity are effect modifiers, using a significance level of 0.10 because the study is not powered for detecting effect modification.

For the process evaluation, descriptive statistics are used describing the use of the Move games based on the Move game calendar over the ten months intervention period and the process evaluation measures. All statistical analyses are performed using IBM SPSS Statistics version 21 and statistical significance level is set at p < 0.05 for detecting main intervention effects and p < 0.10 for detecting effect modifiers.

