## Discussion

This paper describes the design of a trial to test the effects of a family oriented active game intervention on anthropometrics and self-reported behavior among adolescents. As mentioned in the introduction, the current trial on active games contributes to existing literature because it is one of the few adequately powered trials, includes normal weight adolescents, has a relatively long follow up period (ten months) and includes a comprehensive process evaluation. Further, the intervention uses the newest generation of active games and incorporates several motivational elements to encourage (maintenance of) active game play. Several studies have focused on overweight/obese children and showed that an active gaming intervention can result in small effects on BMI or body weight [35,60]. However, as far as we know the current trial is the first well powered RCT including normal weight adolescents. Furthermore, the comprehensive process evaluation will provide important insight into whether adolescents adhere to the active game intervention over a ten month period, whether they enjoy playing active games and the factors that hinder or encourage them to play the active games. This information can help to make future active game interventions more effective.

For the current study we chose to encourage the adolescents in the intervention group to substitute non-active gaming with active gaming as much as possible but at least one hour per week. The potential contribution of active games on prevention of excessive weight gain in adolescents, lies partly in the fact that adolescents are intrinsically motivated to play video games and active game interventions capitalize on this intrinsic motivation. As stated before behavior change is more likely to be maintained if one is intrinsically motivated, which means that one enacts in an activity because of the activity itself, because one enjoys the activity and not because of external factors [25]. Giving adolescents an encouragement to play the active games a minimum amount of time might conflict with this potential intrinsic motivation for active game play. However, it is suggested that only providing active games is not enough to impact physical activity or body weight and it is important to also give an instruction regarding the use of the active games [46,48].

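### The 99 per condition does not follow from the stated inputs: two weight follow-ups with ICC 0.7 need 121, and 99 gives about 72% power, not 80%

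*Protocol article*

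**What the plan says.** The Sample size section powers the primary analysis on a between-group "difference in excess weight gain of 0.5 kg (SD = 1.5 kg") over the follow-up measurements, "with a power of 0.80, alpha .05", and concludes that with "an intraclass correlation coefficient (ICC) for within-subject clustering of observations of 0.7, 99 participants in each condition are needed". Allowing for 20% drop-out, it sets a recruitment target of 119 per condition. It states neither the number of repeated measurements nor whether the test is one- or two-sided.

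The number of measurements can be read from the rest of the article. The anthropometrics section says that height, weight, circumferences and skinfolds "are performed at T_0_, T_4m_ and T_10m_ on pre-scheduled days". Table 1 agrees: the one-month contact is a questionnaire only. Weight therefore has one baseline and two follow-up values.

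On testing, the Statistical analyses section says that "statistical significance level is set at p < 0.05 for detecting main intervention effects" and mentions no one-sided test.

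The power claim is prominent. The Abstract says: "This is the first adequately powered RCT including normal weight adolescents". The Discussion says of the trial that "it is one of the few adequately powered trials".

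**The concern.** Repeated follow-ups reduce the required sample size, but with a within-subject correlation as high as 0.7 a second visit adds little. Going from one follow-up to two should save 15% of the sample. The stated 99 implies a saving of 30%, which is the most that any number of visits could give at this correlation.

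What is at stake is how a null result is read. The article presents adequate power as a distinguishing strength. If the risk of missing the target difference is 28 to 30% rather than 20%, a non-significant finding carries less weight against the intervention than the article implies.

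**Working it through.** **Inputs.** From the Sample size section: difference d = 0.5 kg, SD s = 1.5 kg (stated for weight gain, so taken as the SD of the analysed quantity), power 0.80, alpha 0.05, ICC ρ = 0.7. From Table 1 and the anthropometrics section: T = 2 follow-ups. Assumed: a two-sided test, since the article does not say.

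**Step 1: one follow-up.** n = 2(z₀.₉₇₅ + z₀.₈₀)² s²/d² = 2 × (1.960 + 0.8416)² × 1.5²/0.5² = 141.28 per condition.

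**Step 2: the article's figure.** 141.28 × 0.7 = 98.90, which rounds up to 99. This is the only route found to the stated number. It uses the ICC as the multiplier.

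**Step 3: the multiplier for T follow-ups.** The variance of the mean of T equally correlated follow-ups is s² × [1 + (T − 1)ρ]/T. The factor falls to ρ only as T goes to infinity. For T = 2 it is (1 + 0.7)/2 = 0.85, so n = 141.28 × 0.85 = 120.09, or 121 per condition. (A t-based calculation gives 121.06, or 122.)

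**Step 4: other readings.**

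| Reading | n per condition |
|---|---|
| Two-sided, T = 1 | 142 |
| Two-sided, T = 2 | 121 |
| Two-sided, T = 3 | 114 |
| Two-sided, T = 4 | 110 |
| One-sided, T = 1 | 112 |
| One-sided, T = 2 | 95 |
| One-sided, T = 3 | 90 |
| SD read as cross-sectional, baseline-adjusted, T = 2 / T = 1 | 51 / 73 |
| SD read as cross-sectional, change score, T = 2 / T = 1 | 64 / 85 |

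None gives 99. Two-sided with T = 2, the ICC that would give 99 is 2 × 99/141.28 − 1 = 0.40, not 0.7.

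**Step 5: power for 0.5 kg, averaged over the two follow-ups.**
- 99 per condition: SE = 1.5 × √(2 × 0.85/99) = 0.1966; power = Φ(0.5/0.1966 − 1.960) = 72.0%.
- 95 per condition (119 × 0.8 = 95.2): SE = 1.5 × √(2 × 0.85/95) = 0.2007; power = 70.3%.
- 119 per condition, with nobody lost: 79.6%.
- For comparison, a contrast at 10 months alone with 99 per condition: SE = 1.5 × √(2/99) = 0.2132; power = 65.0%.

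**Step 6: difference detectable with 80% power.** 2.8016 × 0.1966 = 0.55 kg with 99; 2.8016 × 0.2007 = 0.56 kg with 95.

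**The case against.** The arithmetic itself is hard to dispute. The objections concern what it rests on and how much it matters.

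- **Sidedness is not stated, and the hypotheses are directional.** With a one-sided test and two follow-ups, 95 would suffice and 99 would give 81.6% power. This stands as a condition. It does not explain 99, and a plain 0.05 significance level with no mention of one-sided testing is conventionally two-sided.
- **The origin of 99 is inferred.** No formula is shown, and a fuller protocol may contain one. This also stands. The match with 141.28 × 0.7 is close, but it is an inference; the mismatch does not depend on it.
- **The planned model adjusts for baseline and, in model 2, for demographics.** If the covariates correlated at about 0.39 with the outcome, the factor would drop to 0.85 − 0.39² ≈ 0.70 and 99 would give 80%. The article states no such correlation and takes no such credit, so this cannot support its figure. It does mean that 72% is the power under the stated inputs, not necessarily that of the fitted model.
- **Weight gain in kilograms is not a listed primary outcome.** True: those are BMI-SDS, waist-SDS, hip circumference and skinfolds. Correcting the number does not establish power for them. Nor does the stated 99, which is the only support the article gives for its power claims.
- **The 95 is a worst case.** The primary analysis keeps anyone with at least one follow-up, so some who drop out still contribute. The 72% at 99 does not depend on this.
- **The shift is modest.** The detectable difference moves by about a tenth, no estimate is biased, and a null result should be read from its confidence interval. That limits the damage but does not make the stated power correct.

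**Conclusion.** The concern holds. Under a two-sided 0.05 test, two weight follow-ups, ICC 0.7 and SD 1.5 kg for weight gain, 80% power needs 121 per condition. The stated 99 is 22 short. The type II error is about 28% at 99 and 30% at 95, against the stated 20%. Even full retention of all 119 would fall just below 80%, so the whole drop-out allowance is used up by the error.

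The shortfall depends on two-sided testing and on taking the SD as that of weight gain, as written. The failure to reproduce 99 does not: no number of visits in this design returns it under either sidedness or either reading of the SD.

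**What to change.** In the Sample size section, replace the sentence giving 99 with a calculation that a reader can repeat. Suggested content: two-sided alpha 0.05, two follow-ups, ICC 0.7 and variance factor 0.85 require 121 per condition for 80% power; with 99 (95) analysed per condition, power for 0.5 kg is 72% (70%) and the difference detectable with 80% power is 0.55 (0.56) kg.

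If a different formula, sidedness, SD definition or credit for covariate adjustment was used, state it with its inputs so that 99 can be reproduced. Remove or qualify the claims of adequate power in the Abstract and Discussion to match.

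The cost is wording and a less favourable power statement. No further recruitment is needed if the power is restated.

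### The 20% drop-out allowance is calculated as 99 × 1.2 = 119 per condition; at that drop-out rate, 99 completers require 99 / 0.8, or 124

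*Protocol article*

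**What the plan says.** The Sample size section of the protocol article aims to detect a "clinically relevant difference in excess weight gain of 0.5 kg (SD = 1.5 kg) between the intervention and control condition", "with a power of 0.80, alpha .05 and an intraclass correlation coefficient (ICC) for within-subject clustering of observations of 0.7". From these inputs it concludes that "99 participants in each condition are needed". It then allows for loss to follow-up in one sentence: "Taking into account an anticipated drop-out of 20%, a total of 119 adolescents per condition needs to be recruited".

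Two other sections affect what this means in practice. Under Measurements, the anthropometric outcomes are taken at baseline and at two later visits: "skinfolds thickness are performed at T_0_, T_4m_ and T_10m_ on pre-scheduled days". Under Statistical analyses, the primary analysis is restricted as follows: "we analyze those participants which have at least one follow-up measurement in the groups they were randomized to". Multiple imputation for adolescents with only a baseline measurement is a sensitivity analysis. The article gives no other drop-out rate and no other recruitment target.

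**The concern.** The three figures in the Sample size section (99 needed, 20% drop-out, 119 recruited) cannot all hold if the 99 are meant to be those who remain. Taking 20% away from 119 leaves fewer than 99. Adding 20% to the required number is a common slip: the 20% is applied to the number needed at the end, although drop-out acts on the number recruited at the start.

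What is at stake is whether the recruitment target delivers the sample size and power that the same paragraph states. The article presents adequate power as one of the trial's main strengths, in the Abstract and again in the Discussion, so the target should agree with the other figures beside it. The imputation analysis does not repair this, because it does not bring adolescents without follow-up into the primary analysis.

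**Working it through.** **Inputs, all from the Sample size section:** 99 required per condition; drop-out 20%; recruitment target 119 per condition; difference 0.5 kg; SD 1.5 kg; power 0.80; alpha 0.05; ICC 0.7. Sidedness is not stated, so a two-sided test is assumed.

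**1. Reproducing the 119.**
- 99 × (1 + 0.20) = 118.8, rounded up to 119. This matches the article.
- 99 / (1 − 0.20) = 123.75, rounded up to 124. This does not.

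**2. Checking each target against the stated drop-out.**
- 119 × 0.80 = 95.2, about 4 below 99.
- 124 × 0.80 = 99.2, which keeps the 99.
- Highest drop-out at which 119 still leaves 99: 1 − 99/119 = 20/119 = 16.8%.
- Shortfall in recruitment: 124 − 119 = 5 per condition, or 248 − 238 = 10 in total.

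**3. Finding the basis of the 99, so that the loss can be expressed as power.** The article gives no formula. The usual two-sample calculation is

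n = 2 × [1.5 × (1.960 + 0.842) / 0.5]² = 141.28 per condition.

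Multiplied by the stated ICC, 141.28 × 0.7 = 98.9, rounded up to 99. The factor 0.7 is therefore used below only because it reproduces the article's figure.

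**4. Power on that basis.** Power = Φ( 0.5 / [1.5 × √(2 × 0.7 / n)] − 1.960 ).
- n = 99: 0.5 / 0.1784 = 2.803; Φ(0.843) = 80.0%.
- n = 95.2: 0.5 / 0.1819 = 2.749; Φ(0.789) = 78.5% (78.4% at n = 95 exactly).

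The loss is about 1.5 percentage points. Put another way, the difference detectable with 80% power moves from 0.50 kg to 0.5 × √(99/95.2) = 0.51 kg.

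**5. How far the worst case depends on when adolescents leave.** Of 119 recruited, about 24 drop out (119 × 0.20 = 23.8). The 95.2 in step 4 assumes that none of them has a measurement at four or ten months. The gap to 99 is 3.8.
- If a drop-out with only the four-month measurement counts in full, 4 of the 24 close the gap.
- If such a person counts as 0.85 of a completer (variance of the mean of two measurements relative to one at ICC 0.7: (1 + 0.7)/2), 3.8 / 0.85 = 4.5, so 5 close it.
- If such a person counts as 0.7, 3.8 / 0.7 = 5.4, so 6 close it.

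**The case against.** The strongest reply is that the slip barely matters. A loss of about 1.5 points of power is smaller than the uncertainty in the inputs: the article says that the 0.5 kg target was borrowed from adult calculations because none existed for adolescents. That stands, and it is why the point is minor.

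A second reply concerns the number analysed. A reader might infer that the trial will have only 95 per condition in its primary analysis. The documents do not support this as a firm figure. Anthropometrics are taken at both four and ten months, and anyone with at least one of these measurements is kept. The article does not say whether the 20% means loss by ten months or loss before any follow-up. If it means loss by ten months, a handful of the 24 leaving after the four-month visit would restore the equivalent of 99. This reply also stands, so 95 is the worst case. It does not rescue the 119, however: the article makes no allowance for partial follow-up and simply inflates 99 by 20%.

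A third reply is that multiplying by 1.2 is a familiar convention. That has no weight here, because the convention does not deliver the required number at the stated drop-out.

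**Conclusion.** The recruitment target is wrong as written. For 99 completers at 20% drop-out it should be 124 per condition, not 119. This follows from the article's own figures and needs no outside assumption.

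The consequence is minor: 5 recruits per condition, about 95 completers instead of 99, and power of about 78.5% instead of 80% at worst. The power figures rest on three assumptions: a two-sided 0.05 test, the variance factor of 0.7 that reproduces the 99, and no follow-up measurement for any drop-out. If some adolescents leave after four months, the loss is smaller and may vanish.

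A reader might also be tempted to merge this with doubts about how the ICC enters the calculation of 99, and so to infer a much larger loss of power. Nothing in the drop-out step supports that. It takes 99 as given, and the ICC question is separate and has to be argued on its own.

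**What to change.** Either of two changes to the Sample size section settles the point:

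- Correct the target to 124 adolescents per condition (99 / 0.8), 248 in total. The cost is 10 more recruits.
- Keep 119 per condition and state that it leaves 99 completers only up to a drop-out of 16.8%. Add that at 20% drop-out power would be about 78.5% in the worst case of 95 analysed per condition. The cost is one sentence and a slightly lower stated power.

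With either choice, it would help to say whether the 20% means loss by ten months or loss before any follow-up measurement, since that decides how close the trial comes to the worst case.

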### Recruitment

Recruitment of adolescents takes place in four cities in the Netherlands: Amsterdam, Amersfoort, Leiden and Breda. Advertisements are posted on game websites, game magazines, Facebook, newsletter for PlayStation owners and local papers, and announcements are made on local radio. In addition, local health organizations (GGD) and municipalities in the four cities collaborate by providing addresses of families with a child aged 12–16 years old. In Leiden all families with a 12–16 years old child receive an invitation letter, and in Amsterdam, Breda and Amersfoort we make a selection based on postal code areas covering neighborhoods with a relatively low social economic status. Also, flyers are distributed in schools and popular places for gaming adolescents (e.g. game shops, music stores). Interested adolescents and families can provide their contact details on our project website or send it by mail. The interested families are contacted by email and asked to complete an online questionnaire to assess further inclusion criteria. Next, eligible families receive information about participation and an informed consent form that they have to fill in prior to the baseline measure. Then, families receive information about the baseline online questionnaires and an invitation for the adolescent’s baseline assessment.

